## **12.3 Statistical methods**

### **12.3.1 Primary analyses**

Descriptive statistics:

When the "occurrence of either of myocardial infarction, coronary bypass surgery, percutaneous transluminal coronary angioplasty, stroke, carotid endarterectomy, percutaneous transluminal cerebral angioplasty, carotid artery stenting, or death" is defined as an event, the event-free survival period (time to occurrence of either of myocardial infarction, coronary bypass surgery, percutaneous transluminal coronary angioplasty, stroke, carotid endarterectomy, percutaneous transluminal cerebral angioplasty, carotid artery stenting, or death) as well as the annual percentage of subjects remaining event-free are to be calculated by the Kaplan-Meier method, and 95% confidence intervals (CI) calculated using Greenwood's formula.

Hypothesis testing:

A stratified log-rank test adjusting the stratification factors used for dynamic allocation (except for participating institutions) is to be used to verify the hypothesis that event-free survival is longer with intensive therapy than conventional therapy, with the "occurrence of either of myocardial infarction, coronary bypass surgery, percutaneous transluminal coronary angioplasty, stroke, carotid endarterectomy, percutaneous transluminal cerebral angioplasty, carotid artery stenting, or death" defined as an event.

Effect size estimates:

Hazard ratios (intensive therapy/conventional therapy) for the events described above as well as 95% confidence intervals are to be calculated by using the Cox proportional hazards model. The adjustment/stratification factors used for dynamic allocation except for participating institutions are to be incorporated into the regression analysis models. Furthermore, if any background factors are found to potentially affect the estimates, these factors are also to be incorporated into the regression analysis models. Details of the approach to be taken are to be described in the Statistical Analysis Plan.

### **12.3.2 Secondary analyses**

Descriptive statistics:

With either one of the secondary endpoints defined as an event, event-free survival (time to occurrence of a secondary endpoint or death), as well as annual percentage of subjects remaining event-free, is to be calculated by using the Kaplan-Meier method, and 95% confidence intervals (CI) are to be calculated by using the Greenwood's formula.

Hypothesis testing:

A stratified log-rank test adjusting the stratification factors used for dynamic allocation (except for participating institutions) is to be used to verify the hypothesis that event-free survival is longer with intensive therapy than conventional therapy, with either one of the secondary endpoints defined as an event.

When intensive therapy has been proven to be superior to conventional therapy in the secondary analyses, we conclude that intensive therapy is a useful treatment modality. However, as the primary and secondary endpoints are not independent of one another, the statistical inference is to be adjusted for multiplicity by using the re-sampling method. Strictly speaking, this adjustment method has the potential to increase Type 1 error for the entire study. However, as it maintains the Type 1 error for the primary endpoints at an appropriate level (5%, two-sided), the adjustment method was deemed valid.

Effect size estimates:

Hazard ratios (intensive therapy/conventional therapy) for the events described above as well as 95% confidence intervals are to be calculated by using the Cox proportional hazards model. The adjustment/stratification factors used for dynamic allocation except for participating institutions are to be incorporated into the regression analysis models. Furthermore, if any background factors are found to potentially affect the estimates, after review of the relevant data with the allocation code blinded, these factors are also to be incorporated into the regression analysis models.

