Of these, onset or progression of nephropathy is also considered an important event; therefore, the current trial is to verify the superiority of intensive therapy over conventional therapy with regard to this event-free survival. In the event that intensive therapy has been proven to be superior to conventional therapy in secondary endpoint 1, we conclude that intensive therapy is a useful therapeutic modality. As the primary and secondary endpoints are not independent of one another, the statistical inference is to be adjusted for multiplicity by using the re-sampling method.

Of note, secondary endpoint 2 was included to complement the primary endpoints. Therefore, only exploratory analysis is to be performed on this endpoint and not to be used as a rationale for the main conclusions to be drawn. In other words, whether or not intensive therapy is superior to conventional therapy in reducing macrovascular complications is to be determined on the basis of an analysis of the primary endpoints.

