## **12.4 Interim Analyses and the Clinical Trial Review Committee**

### **12.4.1 Interim analyses**

To assess whether the main objectives of the study have been achieved, 3 interim analyses were planned as follows. These analyses were to be performed by independent statistical analysts at the Data Center.

- Early after completion of the subject study registration
- 1 year after completion of the subject study registration
- 2 years after completion of the subject study registration

However, as the general survey conducted in June 2006 demonstrates that fewer subjects had been accrued to date and fewer events were reported than initially expected, interim analyses are to be performed based the nine general surveys scheduled to place at the following time points:

- December 2007
- December 2008
- December 2009
- December 2010
- June 2011
- June 2012
- June 2013
- June 2014
- June 2015

Data reviewed by the Endpoint Assessment Committee are to be used for analysis at each of the interim analyses. Unless otherwise notified, the study subjects are to continue their study registration even during the interim analyses. Once the interim analysis results have demonstrated that the main objectives of the study have been achieved, the trial is to be discontinued and the study results to be released.

To reduce the Type 1 error associated with the multiple analyses (interim and final analyses) and to maintain the two-sided Type 1 error at 5%, analyses of the primary endpoints are to be adjusted for multiplicity by using a Lan-DeMets alpha function approach with an alpha -spending function of the O'Brien-Fleming type. In addition, Bayesian Probability or conditional power is to be calculated as reference data.

Of the secondary endpoints, "time to onset or progression of nephropathy or occurrence of death" is to be analyzed with adjustment by the re-sampling method for multiplicity in relation to the primary endpoints. No inter-group comparisons are to be made except this endpoint, unless the Trial Assessment Committee or the Central Ethics Committee approves such comparison.

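### A secondary endpoint may carry the conclusion that intensive therapy is useful without primary success, so that conclusion is not held at 5%, and the protocol contradicts itself on which secondary endpoint is meant

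*Protocol*

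**What the plan says.** **Two routes to one conclusion.** Section 12.1 concludes that intensive therapy is useful when the primary null hypothesis is rejected. It then allows the same conclusion if intensive therapy is shown to be "superior to conventional therapy in secondary endpoint 1, we conclude that intensive therapy is a useful therapeutic modality". Section 12.3.2 repeats this for the secondary analyses in general: "When intensive therapy has been proven to be superior to conventional therapy in the secondary analyses, we conclude that intensive therapy is a useful treatment". Neither place requires the primary to succeed first.

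**How multiplicity is handled.** In section 12.3.2, "the statistical inference is to be adjusted for multiplicity by using the re-sampling method". The section then says "Strictly speaking, this adjustment method has the potential to increase Type 1 error for the entire study", and defends the choice: "However, as it maintains the Type 1 error for the primary endpoints at an appropriate level (5%, two-sided), the adjustment method was deemed valid".

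**Interim looks.** Section 12.4.1 schedules nine interim analyses before the final one. It says "analyses of the primary endpoints are to be adjusted for multiplicity by using a Lan-DeMets alpha function approach", with O'Brien-Fleming-type spending. Nephropathy or death is the one secondary comparison allowed by default at the interims. The only adjustment stated for it is re-sampling in relation to the primary.

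**Status of the secondary endpoints.** The list in section 12.1 numbers myocardial infarction, stroke or death as 1 and nephropathy as 2. The text below the list says superiority on nephropathy is to be verified, makes endpoint 1 the route to the conclusion, and says of endpoint 2 that "only exploratory analysis is to be performed on this endpoint and not to be used as a rationale for the main conclusions to be drawn". Section 12.3.3 calls the secondary-endpoint analyses exploratory and leaves them unadjusted.

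**The concern.** If either of two tests can support a conclusion and the first already uses the whole 5%, any chance given to the second is added on top. Re-sampling the secondary p-value makes that addition smaller but cannot remove it. The defence in section 12.3.2 answers a different question: it shows that the primary claim is protected, not that the shared conclusion is.

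What is at stake is a trial that misses its primary endpoint and still declares the strategy useful on a secondary result, at an error rate the protocol does not state. The risk is greater because the protocol does not settle which secondary endpoint could be used in this way, or whether its p-value would be adjusted at all.

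**Working it through.** **Inputs from the protocol:** primary at 5% two-sided (12.3.2, 12.4.1); Lan-DeMets spending of O'Brien-Fleming type for the primary, nine interims plus a final analysis (12.4.1); re-sampling adjustment of the secondary (12.3.2); 250 events (section 13).

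**Assumptions not in the protocol:** correlation ρ between the two log-rank statistics from 0 to 0.9; a max-T critical value to represent the re-sampling method; information fractions for the repeated looks.

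**1. The plan's own 5%.** With cumulative spending 4[1 − Φ(2.241/√t)], the spend at t = 1 is 4 × 0.0125 = 0.0500. Simulating ten looks gives 0.049 to 0.050. The primary alone is held at 5%.

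**2. Primary at full 5%, one adjusted secondary test at the end.** The adjusted critical value c solves P(|Z1| < c, |Z2| < c) = 0.95. The error rate for the shared conclusion is

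P(|Z1| > 1.96 or |Z2| > c) = 0.05 + P(|Z1| ≤ 1.96, |Z2| > c).

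The second term is positive for any finite c, short of perfect correlation. At ρ = 0 the secondary has nominal level 1 − √0.95 = 0.0253, so the total is 1 − 0.95 × √0.95 = 0.0741. In the benefit direction it is 1 − 0.975 × (1 − 0.01266) = 0.0373.

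| ρ | c | Two-sided | Benefit direction (nominal 2.5%) |
|---|---|---|---|
| 0 | 2.236 | 7.4% | 3.7% |
| 0.7 | 2.180 | 6.8% | 3.4% |
| 0.9 | 2.108 | 6.1% | 3.1% |

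**3. Same test, unadjusted, as section 12.3.3 would have it.** At ρ = 0 the total is 1 − 0.95² = 0.0975. Over ρ from 0 to 0.9 it runs from 9.8% down to 7.2%.

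**4. Which endpoint is confirmatory.**

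- 12.1, opening statement on nephropathy: superiority to be verified.
- 12.1, route to the conclusion: endpoint 1, which is myocardial infarction, stroke or death in the list.
- 12.1, endpoint 2, which is nephropathy in the list: exploratory.
- 12.3.2: the secondary analyses, with no endpoint singled out, and adjusted.
- 12.3.3: secondary endpoints exploratory and unadjusted.
- 12.4.1: nephropathy or death compared at the interims, adjusted against the primary.

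These cannot all stand. The two numbers in 12.1 may have been swapped, since an endpoint said to complement the primary sounds more like myocardial infarction, stroke or death. The document does not say so.

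**5. Repeated looks at nephropathy (conditional).** Suppose nephropathy is tested at all ten looks at the ρ = 0 adjusted level of 0.0253, with nothing added for time. With information fractions 0.05, 0.14, 0.26, 0.39, 0.45, 0.57, 0.68, 0.80, 0.92 and 1, its own error rate is about 11.6%. With ten equal steps it is about 10.8%. The unequal fractions follow the plan's survey dates and assume a constant hazard reaching 250 primary events by March 2016. The protocol gives no nephropathy event rate.

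**The case against.** **The trade-off is disclosed.** The protocol ties its 5% to the primary endpoint, says openly that study-wide error may rise, and in 12.1 reserves the macrovascular conclusion for the primary analysis. All of this is correct, and that claim is not inflated. It does not rescue the broader conclusion of usefulness, which 12.1 and 12.3.2 attach to either route.

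**The two-sided figures overstate a false claim of benefit.** The alternative is directional, and 12.4.1 says no test is made when the event rate is higher under intensive therapy. This stands, so the benefit-direction figures are given as well. At 3.1% to 3.7% against 2.5%, the excess is modest but real.

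**Nephropathy is not the settled second route.** A reader might infer that nephropathy alone could carry the conclusion after ten looks with no alpha spending, giving a combined rate of about 15% to 17%, or 20% to 25% with each nephropathy look at 1.96. The document does not support that as a finding, for four reasons:

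- Read literally, 12.1 makes endpoint 1 the route and nephropathy exploratory.
- Section 12.4.1 does not say what level applies to nephropathy at each look, and defers detail to an Interim Statistical Analysis Plan that is not at hand. If the adjusted p-value were held to half the primary's nominal level at each look, the combined rate would be about 5.7% to 7.5%.
- Testing each look at 1.96 would ignore the re-sampling adjustment that 12.4.1 does state.
- Section 13 says no interim analysis aimed at demonstrating superiority has been conducted, so the looks are scheduled, not shown to have been used.

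**Conclusion.** The point holds for the rule as written. Whichever secondary endpoint is meant, an ungated second route beside a primary at its full 5% puts the error rate for the conclusion of usefulness above 5%. It is about 6.1% to 7.4% two-sided, or 3.1% to 3.7% in the benefit direction, for one adjusted secondary test at the end. The range rests on assumed correlations of 0.9 to 0 and a max-T form of re-sampling; the direction of the excess does not depend on which of these correlations is taken.

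The contradiction over which secondary endpoint is confirmatory, and whether it is adjusted, is a separate defect that stands on the text alone.

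The repeated-look figure of about 11.6% is for nephropathy by itself, not the trial-wide rate. It applies only if the unseen interim plan adds no adjustment across looks, and it borrows the primary's information fractions.

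**What to change.** Amend sections 12.1, 12.3.2, 12.3.3 and 12.4.1 together:

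- Name one confirmatory secondary endpoint, by its content as well as its number, and use it consistently. Call the others exploratory.
- Test that endpoint only once the primary has crossed its boundary, against its own O'Brien-Fleming-type spending boundary at two-sided 5%.
- If the primary does not cross, report the endpoint descriptively, with no conclusion of usefulness.
- Delete the sentences in 12.1 and 12.3.2 that allow the conclusion from a secondary endpoint alone, and the passage in 12.3.2 that accepts the higher study-wide error.
- Remove the confirmatory nephropathy comparison from interims at which the primary has not crossed.

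The cost is wording. Primary power is unchanged, and the error rate for the conclusion returns to 5.0%. The downside is that a secondary endpoint alone can no longer carry the conclusion.

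If an independent second route is wanted, giving each endpoint 2.5% with its own spending also holds the total, at 3.7% to 4.9% over the same correlations. It costs primary power. With 250 events, a fixed-design approximation and the protocol's rate ratio of 0.70 (3.08/4.4), power is Φ(0.3567 × √250 / 2 − 1.96) = 80.5%. Replacing 1.96 by 2.241 gives about 72%.

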### **12.3.3 Other analyses**

To complement analyses of the primary endpoints, three kinds of analyses (descriptive statistics, hypothesis testing and effect size estimates) are to be performed on the secondary endpoints. However, being exploratory in nature, these analyses are not to be adjusted for multiplicity.

Fisher's direct exact probability estimation is to be used to compare the percentages of occurrence of adverse reactions between the two treatment arms as part of the safety evaluation, and 95% confidence intervals (CI) for the differences detected. Accurate confidence intervals are to be estimated based on the bimodal distribution of the data.

Otherwise, exploratory analyses are to be performed as required. When such analyses are to be performed, their details

are to be described in the Statistical Analysis Plan.

## **12.4 Interim Analyses and the Clinical Trial Review Committee**

### **12.4.1 Interim analyses**

To assess whether the main objectives of the study have been achieved, 3 interim analyses were planned as follows. These analyses were to be performed by independent statistical analysts at the Data Center.

- Early after completion of the subject study registration
- 1 year after completion of the subject study registration
- 2 years after completion of the subject study registration

However, as the general survey conducted in June 2006 demonstrates that fewer subjects had been accrued to date and fewer events were reported than initially expected, interim analyses are to be performed based the nine general surveys scheduled to place at the following time points:

- December 2007
- December 2008
- December 2009
- December 2010
- June 2011
- June 2012
- June 2013
- June 2014
- June 2015

Data reviewed by the Endpoint Assessment Committee are to be used for analysis at each of the interim analyses. Unless otherwise notified, the study subjects are to continue their study registration even during the interim analyses. Once the interim analysis results have demonstrated that the main objectives of the study have been achieved, the trial is to be discontinued and the study results to be released.

To reduce the Type 1 error associated with the multiple analyses (interim and final analyses) and to maintain the two-sided Type 1 error at 5%, analyses of the primary endpoints are to be adjusted for multiplicity by using a Lan-DeMets alpha function approach with an alpha -spending function of the O'Brien-Fleming type. In addition, Bayesian Probability or conditional power is to be calculated as reference data.

Of the secondary endpoints, "time to onset or progression of nephropathy or occurrence of death" is to be analyzed with adjustment by the re-sampling method for multiplicity in relation to the primary endpoints. No inter-group comparisons are to be made except this endpoint, unless the Trial Assessment Committee or the Central Ethics Committee approves such comparison.

In the event that the interim analysis results have demonstrated the superiority of intensive therapy over conventional therapy, as a general rule, the trial is to be discontinued. When the event rate has been shown to be higher with intensive therapy than with conventional therapy, the hypothesis is not to be tested, and the overall decision as to the termination of the trial is to be made.

A detailed Interim Statistical Analysis Plan is to be jointly developed by the Clinical Research Leader, Trial Secretariat Office, trial statisticians and independent statistical analysts through mutual consultation. The independent statistical analysts are not to be involved in the revision of the Statistical Analysis Plan or the Patient Accrual Goal that may occur after the first interim analysis.

### **12.4.2 Reporting on/review of statistical analyses**

The independent statistical analysts are to draft and submit the interim analysis reports to the Trial Assessment Committee, which is in turn to make its decision as to the continuation of the study, and to make its recommendations to the Principal Investigator, the Foundation Secretariat, and the Clinical Research Leader.

Unless the Trial Assessment recommends discontinuing the study, no personnel except for the Trial Assessment Committee is to be given access to the results of the interim analyses. The Trial Assessment Committee is obliged not to disclose the interim analysis data to any personnel outside the Trial Assessment Committee. However, the Clinical Research Leader is to be construed as forming part of the Trial Assessment Committee.

The Clinical Research Leader is to make the decision as to whether the trial is to be continued or discontinued or the trial protocol is to be revised in part, on the recommendation of the Trial Assessment Committee. In the event that the trial is to be discontinued or the trial protocol is to be revised in part, the Clinical Research Leader is to submit a "request for early termination of the trial" or "request for the revision of the trial protocol" in writing. The Operations Committee is to review the request, and to obtain the approval of the Central Ethics Committee if the Trial Administrative Committee is to decide to revise the trial protocol in part. Upon approval by the Central Ethics Committee, the Clinical Research Leader is to be entitled to revise the trial protocol as requested.

The Clinical Research Leader is to be entitled to raise an objection to the recommendations of the Trial Assessment Committee. The Trial Assessment Committee is to be entitled to make its recommendations again after deliberations. In the event of failure to harmonize the views between the Clinical Research Leader and the Trial Assessment Committee, The Trial Administrative Committee is to make a final decision as to the continuance or discontinuance of the trial or revision of the trial protocol.

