The final number of subjects who enrolled in the study during the registration period was 2,542 patients. Based on a patient accrual period of 2.5 years with a follow-up period of 4.25 years, the power of the test will be  $\geq 80\%$  with a 5% level of significance (2-sided). Therefore, the expected number of events will be changed to 250 because an interim analysis aimed at demonstrating the superiority of intensive therapy over conventional therapy in order to discontinue the trial, has not been conducted.

The rate of occurrence was lower than what was expected before the start of the study, suggesting the number of events would not reach the required number of events during the predefined follow-up period. Since the registration period was expired, addition of subjects was impossible. Thus, follow-up period was extended for a sufficient time until the required number of events could be obtained.

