### **19.5 Trial Assessment Committee**

The Trial Assessment Committee is to provide interim reports (evaluations of interim analyses) on the progression of the trial in view of the recommendations it is to make regarding the continuation of the trial or release of the study results while being in close contact with the Trial Progress Management, and to make recommendations regarding the measures and actions to be taken to the Principal Investigator, the JD-PMIRC Secretariat, and the Clinical Research Leader.

The Chairperson of the Committee is to be chosen by the members of the Committee from among the members of the Committee. The Chairperson of the Committee is to convene members of the Committee and to serve as Chairperson. Meetings by the Committee are to be held with the JF-PMIRC Secretariat, Trial Progress Management members, the Clinical Research Leader and Clinical Research Leader-appointed personnel (including the independent statistical analyst) attending, in addition to the members of the Trial Assessment Committee.

The Chairperson is to appoint a committee member in charge of the meeting minutes prior to the meeting, where the Chairperson may combine this role. Prior to deliberations of a particular research issue, the Clinical Research Leader is to provide an outline of the issue, along with any new developments with the issue. Members of the Trial Progress Management are to report on the status of trial monitoring. Prior to deliberations, all members of the Trial Assessment Committee and the independent statistical analyst are to excuse themselves, and the independent statistical analyst is to account for the interim analysis results and evaluate the results. The Trial Assessment Committee is to make its recommendations as to the "early termination" or "continuation" of the study after its consensual decision making. If the decision was divided, the decision is to be made by a majority vote, where in the case of a tie the Chairperson is to cast a tie-breaking vote. The committee member in charge of the meeting minutes is to summarize the results of deliberations,

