and to seal these minutes together with the interim analysis results. After deliberations, the Committee is to notify the Principal Investigator, the JF-PMIRC Secretariat, and the Clinical Research Leader of their recommendations. The interim analysis results and the minutes of the Committee deliberations thus sealed are not to be unsealed for disclosure until trial termination is recommended or until the completion of the final analysis.

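### Protocol 12.4.2 counts the Clinical Research Leader as part of the committee that sees interim results; 19.5 treats the Leader as an outsider, and no bar on later revisions covers the Leader

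*Protocol*

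**What the plan says.** **Access.** Section 12.4.2 states that, unless the committee recommends stopping, "no personnel except for the Trial Assessment Committee is to be given access to the results of the interim analyses". It binds the Trial Assessment Committee not to disclose the data outside itself. The next sentence reads: "However, the Clinical Research Leader is to be construed as forming part of the Trial Assessment Committee".

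**Meetings.** Section 19.5 describes meetings held with the secretariat, Trial Progress Management, and the "Clinical Research Leader and Clinical Research Leader-appointed personnel (including the independent statistical analyst) attending, in addition to the members of the Trial Assessment Committee". On the closed part it says: "Prior to deliberations, all members of the Trial Assessment Committee and the independent statistical analyst are to excuse themselves". The committee then notifies the Principal Investigator, the secretariat and the Leader of its recommendation. The results and minutes "thus sealed are not to be unsealed for disclosure until trial termination is recommended or until the completion of the final analysis".

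**Bar on later involvement.** Section 12.4.1 says: "The independent statistical analysts are not to be involved in the revision of the Statistical Analysis Plan or the Patient Accrual Goal", for revisions after the first interim analysis. No other role is named.

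**The concern.** Someone who knows the observed treatment difference should not take part in choices that shape the final comparison. The Lan-DeMets spending approach in 12.4.1 allows flexible timing of looks, but it holds the two-sided 5% error only if timing, event target and follow-up are chosen without regard to that difference. The same applies to rulings on who belongs in the primary analysis set.

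The trial is open-label (6.1) and 12.4.1 schedules nine interim analyses, from December 2007 to June 2015. A Leader who saw comparative results at those looks could be influenced in continuation decisions, revision requests, plan drafting and eligibility rulings. Knowledge of the results could also affect trial conduct at the sites. The protocol appears to recognise this kind of risk, since it keeps the independent analysts out of later plan and accrual revisions. It leaves the same gap open for a role with far more authority.

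**Working it through.** The main check is textual: who may see results, and what the Leader may do afterwards.

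**1. Is the Leader inside or outside?**
- Inside: 12.4.2. The sentence follows directly on the non-disclosure duty and opens as a qualification of it, so its natural effect is to exempt the Leader.
- Outside: 19.5 names the Leader among attendees additional to the members, has the committee notify the Leader, and seals the results. Section 12.4.2 itself has the committee make recommendations to the Leader and lets the Leader object to them, which suits an outside recipient.

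The two positions cannot both operate. If the Leader is a member, sealing the results does not keep them from the Leader. If the Leader is not a member, the 12.4.2 sentence has no purpose.

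**2. Does the closed session settle it?** No. Read literally, "all members of the Trial Assessment Committee and the independent statistical analyst are to excuse themselves", yet the same sentence goes on to have the analyst explain the interim results. The wording defeats itself and cannot be used to decide who stays.

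**3. What can the Leader do?**

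| Activity | Section | Leader's part | Blinding or bar stated for the Leader |
|---|---|---|---|
| Continue, stop or revise on the committee's recommendation | 12.4.2 | Decides and files the request; may object. Requests are reviewed, revisions need Central Ethics Committee approval, and unresolved disputes go to the Trial Administrative Committee | None |
| Revise or stop for other reasons | 18.2 | Initiates, consulting four committees | None |
| Interim Statistical Analysis Plan | 12.4.1 | One of four parties | None |
| Eligibility for the primary analysis set | 12.2 | One of three parties | None |
| Request to extend accrual or follow-up, or raise accrual, if events fall short | 13 | Not named: Trial Secretariat, trial statisticians, Central Ethics Committee | Not applicable |

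The protocol does state blinding elsewhere: 12.3.2 requires the review of background factors for the secondary models to be done with the allocation code blinded. Section 12.2 has no such condition.

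**4. Does the revised event target need interim data to explain it?** Inputs are the annual rates, two-sided 5% level and power in section 13, with 1:1 allocation. Schoenfeld's formula is d = 4(z_α/2 + z_β)² / (ln HR)².
- HR = 3.08/4.4 = 0.70 at 90% power: 4(1.960 + 1.282)² / 0.3567² gives 331 events. HR = 1.5347/2.2 = 0.6976 gives 325. The stated 328 is reproduced.
- At 80% power (z_β = 0.842), the same hazard ratios give 247 and 243.
- Power at 250 events is Φ(√250/2 × |ln HR| − 1.960): 80.5% at HR 0.70 and 81.3% at HR 0.6976. This matches the stated power of at least 80%.

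The figure of 250 therefore follows from the design hazard ratio with power lowered from 90% to 80%. No observed difference is needed to arrive at it.

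**The case against.** The strongest reply is that the protocol does not in substance unblind the Leader. Section 19.5, the fuller description of the committee, treats the Leader as a non-member and seals the results. Its recusal sentence is evidently a drafting or translation slip for the opposite meaning. The Leader's powers are also limited: the interim plan and eligibility rulings are shared, revisions need Central Ethics Committee approval, and 12.2 repeats the tests in all registered subjects, which would expose any effect of eligibility rulings. Most of this stands. It shows that the Leader is not established as unblinded and does not act alone. It does not remove the 12.4.2 sentence, which grants access in plain terms, and it supplies no bar if that access is used.

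Three stronger readings are tempting, and the document does not support them.
- A reader might infer that the Leader sets the event target. Section 13 routes event-shortfall requests through the Secretariat, trial statisticians and Central Ethics Committee, and names nobody as having chosen 250. The Leader is connected only through the general revision powers in 12.4.2 and 18.2.
- A reader might infer that the move from 328 to 250 was made with knowledge of interim results, because two scheduled dates precede the March 2009 close of accrual. Scheduled dates do not show that comparisons were run or seen. Section 13 states: "the expected number of events will be changed to 250 because an interim analysis aimed at demonstrating the superiority of intensive therapy", and completes the sentence by saying that no such analysis had been conducted. That statement is undated and sits awkwardly with the schedule in 12.4.1, but it is the stated reason. The section also cites final enrolment of 2,542, closed registration and a low event rate.
- A reader might take 19.5 literally and conclude that the Leader, the secretariat and Trial Progress Management stay for the results. The sentence is incoherent on that reading, and 19.6 excludes interim analyses from Trial Progress Management's remit and gives it endpoint data with arms masked.

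**Conclusion.** The point holds as an internal contradiction with a missing safeguard. Section 12.4.2 admits the Leader to the group with interim access, 19.5 treats the Leader as outside it, and the closed-session wording resolves nothing. The bar in 12.4.1 covers only the independent analysts. If the 12.4.2 sentence operates as written, a person with comparative data could take part in continuation, revision, interim-plan and eligibility decisions without restriction.

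No error inflation can be quantified from the document. Any figure would require assumptions about how a person with access would act, and about critical values departing from the O'Brien-Fleming-type spending that 12.4.1 prescribes. The conclusion rests on the text alone. It does not assume that the Leader saw any interim result or that any decision was influenced by one.

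**What to change.** 1. **12.4.2:** delete the sentence that construes the Leader as part of the Trial Assessment Committee.
2. **19.5:** replace the closed-session sentence with wording such as: *Before comparative interim results are presented, everyone except the members of the Trial Assessment Committee and the independent statistical analyst leaves. The Clinical Research Leader attends open sessions only.*
3. **12.4.1:** extend the existing bar: *No person who has seen comparative interim data takes part in revising the Statistical Analysis Plan, the accrual goal, the event target or the follow-up period, or in eligibility rulings under 12.2.*

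With the first two changes the Leader can keep the roles in 12.2, 12.4 and 18.2, because the Leader no longer has access that would trigger the bar. The cost is protocol and committee wording. The downside is that the Leader must act on the committee's recommendation without seeing the interim data behind it.
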